### The second secondary aim

Other secondary clinical outcome measures include the intensity of depressive symptoms, patient functioning, symptom severity (CGI-S), the range of improvement (CGI-I), and the level of insight.

Patients will also undergo dietary assessments at the beginning of the study. This will enable control of that possible confounder at the level of statistical analysis.

To address the third research question about the correlates of the observed change, a number of assessments are planned. Structural changes of the brain, i.e. cortical thickness and fractional anisotropy of the white matter bundles, will be measured using magnetic resonance imaging with tensor diffusion. The level of PUFA metabolites (mainly prostaglandins E2 and D2) will be measured indirectly by using a niacin flush skin test (NFST) described in detail elsewhere by Smesny et al. [76] Oxidative stress and defense will be measured by the total oxidative plasma capacity and 8-epi-alpha-izoprostanes. Neuroplasic changes of the brain will be assessed indirectly by measuring the plasma level of brain-derived neurotrophic factor (BDNF).

Metabolic syndrome components, i.e. weight, body mass index (BMI), waist circumference, serum cholesterol concentration (total, LDL, HDL), serum triglyceride level, systolic and diastolic blood pressure will also be measured during study visits. Descriptive variables will include socioeconomic and demographic variables, variables concerning psychiatric therapy and symptom duration, as well as medical history.

### Study visits

A total of 9 visits will be conducted, including a baseline visit preceding commencement of study medication, followed by 8 follow-up assessments at weeks 1, 2, 4, 6, 8, 16, 26, 52. Clinical assessments and measurements comprising PANSS, CDSS, CGI-S, CGI-S, GAF, Questionnaire of Insight, and metabolic syndrome components, i.e. weight, body mass index (BMI), waist circumference, serum cholesterol concentration (total, LDL, HDL), serum triglyceride level, systolic and diastolic blood pressure will be carried out during the study visits. Correlates of change will also be assessed, i.e. structural brain changes assessed by means of MRI and biochemical measures of oxidative stress and defense, as well as plasma BDNF concentration. The complete schedule of assessments planned in the OFFER trial is presented in Table 1.

**Table 1 Tab1:** **Schedule of the study visits and planned assessments in OFFER trial**

**ID**	**Variable**	**Study visits**	**V1**	**V2**	**V3**	**V4**	**V5**	**V6**	**V7**	**V8**	**V9**
		**Week**	**0**	**1**	**2**	**4**	**6**	**8**	**16**	**26**	**52**
1	Clinical measures	PANSS	X	X	X	X	X	X	X	X	X
		CGI-S	X	X	X	X	X	X	X	X	X
		CGI-I	X	X	X	X	X	X	X	X	X
		CDSS	X	X	X	X	X	X	X	X	X
		GAF	X	X	X	X	X	X	X	X	X
2	Insight questionnaire	“My thoughts and feelings”	X					X		X	X
3	Prostaglandin synthesis (PGD2, PGE2)	Niacin flush skin test	X					X		X	
4	Cognitive function tests: Working memory and Executive functions	TMT Part A and B, and their alternate forms, i.e. Part C, D and Digit Span Forward and Backward	X					X		X	
	Verbal memory	CVLT	X					X		X	
	Visual memory	BVRT	X					X		X	
	Abstract thinking	Halstead Category Test	X					X		X	
	Verbal fluency	Semantic and Phonological	X					X		X	
5	Magnetic Resonance Imaging	Grey matter thickness - VBM	X							X	
		Fractional anisotropy – DTI	X							X	
6	Oxidative stress	Isoprostane 8-epi-PGF2alpha (plasma)	X					X		X	
	Antioxidative defense	Total plasma antioxidative capacity	X					X		X	
7	Neuronal plasticity	Plasma BDNF concentration	X					X		X	
8	Dietary questionnaire	Diet history questionnaire	X								
9	Metabolic syndrome traits	Plasma lipid profile	X					X		X	X
	(biochemical assessments)	Fasting Blood Glucose level	X					X		X	X
10	Metabolic syndrome traits	Body weight	X	X	X	X	X	X	X	X	X
		Waist circumference	X	X	X	X	X	X	X	X	X
	(clinical measures)	Blood pressure	X	X	X	X	X	X	X	X	X

**Abbreviations**: **PANSS** – Positive and Negative Syndrome Scale, **CGI-S** - Clinical Global Impressions - Severity, **CGI-I** - Clinical Global Impressions - Improvement, **CDSS** - Calgary Depression Scale for Schizophrenia, **GAF** – Global Assessment of Functioning, **PGD2** – Prostaglandin D2, **PGE2** - Prostaglandin E2, **TMT** – Trail Making Test Part, **CVLT** – California Verbal Learning Test, **BVRT** - Benton Visual Retention Test , **VBM** – Voxel Based Morphometry, **DTI** –Diffusion tensor Imaging, **8epiPGF2alpha** – plasma concentration of prostaglandin 8-epi-F-2alpha, **BDNF** – plasma concentration of brain derived neurotrophic factor.

### Statistical methods and analytic plan

#### Primary aim

The primary aim is to assess the efficacy of add-on n-3 PUFA therapy in reducing the severity of symptoms in schizophrenia patients after 26 weeks supplementation accompanying standard antipsychotic treatment. Hence, our primary outcome measure is the change observed over time on the total and subscale PANSS scores. The changes in the scores will be calculated by subtracting baseline from follow-up score at each follow-up assessment visit for each patient. Efficacy analyses will be performed using the modified intent-to-treat (ITT) population, which will consist of all randomized patients who will receive at least one daily dose of either placebo or active compound and have at least one efficacy evaluation on day seven or later. Observed case analysis will also be performed for the primary and secondary outcome measures.

Comparisons between treatment groups at baseline will be conducted using a one-way analysis of covariance, with intervention type as a term in the model and duration of untreated psychosis (DUP) as covariate. The distribution of socio-demographic characteristics in the two treatment arms will also be compared to assess the effectiveness of the randomization procedure.

To deal with missing values in our ITT sample, a multiple imputation technique will be used, in which a number of data sets are created, each with the missing values replaced by some plausible values. The imputation of the missing values is based on maximum likelihood and Bayesian procedures and is performed by appropriate algorithms. After the missing cases are completed by several sets of plausible values to create multiple completed datasets, standard complete-data procedures are applied to each completed dataset, and finally the multiple sets of results are combined to yield a single inference. The multiple imputation technique is considered superior to and less biased than the Last Observation Carried Forward (LOCF) [53,77].

The analysis of covariance (ANCOVA) with intervention type as term and baseline PANSS score as covariate will be used to assess the change from baseline in PANSS scores to week 8 and 26 separately. If the overall ANCOVA of the baseline-to-endpoint change score will be significant, pairwise comparison will be performed using Dunnett t test. Analyzes will be two-sided for both ANCOVA and Dunnett test with the type I error rate for rejecting null hypothesis set at 0.05. The same analyses will be repeated to assess the significance of differences in changes of CDSS, CGI and GAF scores between the study arms.

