### Primary outcome measure

The primary outcome measure will be the efficacy of n-3 PUFA in reducing psychopathology in first-episode schizophrenia. The Positive and Negative Syndrome Scale [64] will be used to assess the efficacy of EPA + DHA supplementation in reducing symptom severity in first-episode schizophrenia after 8 and 26 weeks of supplementation. The main outcome measure will be the change in symptom severity from baseline to week 26. Baseline PANSS total score will be subtracted from PANSS score obtained after 26 weeks, resulting in the degree of change observed in the study.

Another way of assessing the efficacy of n-3 PUFA in reducing symptom severity in first-episode schizophrenia patients will be the comparison of the number of responders in each intervention group: 25% and 50% decreases in PANSS total score are considered cut-offs for clinically significant symptom reduction and indicates minimal and great improvement [73]. The percentage change of scores will be calculated according to Leucht et al. [73], based on the principle that a patient with no psychopathological symptoms scores 1 in all PANSS scale items. The formula for calculating change will be as follows: [(Pt2 – N) – (Pt1 – N)/(Pt1 – N)]•100, where Pt1 is the PANSS subscale score at the beginning of the study, Pt2 is the value at the end of the study and N is the number of PANSS subscale items. N = 7 for PANSS positive and negative subscales, N = 16 for the general psychopathology PANSS subscale and N = 30 for the total PANSS score. Patients who achieve at least a 25% reduction in the total PANSS score will be regarded as responders. Those who achieve a 50% decrease will be regarded as much improved.

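### The primary outcome is defined in two conflicting ways and tested at two visits, so the false-positive rate of a primary claim depends on which section governs

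*Protocol article*

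**What the plan says.** The protocol article describes the primary outcome in two places.

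- **Primary outcome measure.** "The main outcome measure will be the change in symptom severity from baseline to week 26". The score is then fixed: "Baseline PANSS total score will be subtracted from PANSS score obtained after 26 weeks". That is one score at one visit. The same section also speaks of "reducing symptom severity in first-episode schizophrenia after 8 and 26 weeks of supplementation", and adds a responder comparison with 25% and 50% cut-offs.
- **Statistical methods and analytic plan, Primary aim.** The stated aim refers to 26 weeks of supplementation, but the section goes on: "our primary outcome measure is the change observed over time on the total and subscale PANSS scores". Change is to be calculated at every follow-up visit. An ANCOVA with baseline PANSS as covariate "will be used to assess the change from baseline in PANSS scores to week 8 and 26 separately". On error control: "Analyzes will be two-sided for both ANCOVA and Dunnett test", "with the type I error rate for rejecting null hypothesis set at 0.05".

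Neither section states an order of testing or an adjustment across scores or visits. The Power calculation section works with a single two-sided 0.05.

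**The concern.** The two sections do not describe the same primary outcome. One gives PANSS total at week 26. The other gives total and subscale scores over time, with formal tests at two visits. The responder formula in the Primary outcome measure section lists three subscales (positive, negative, general psychopathology), so the analytic plan can be read as up to 4 scores × 2 visits = 8 tests, each at 0.05.

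If the report could follow either section, the primary claim could rest on whichever score or visit turned out significant. The stated 0.05 would then describe each single test and not the claim as a whole. This is a conflict between two statements in the document. It is not a complaint that a multiplicity section is missing.

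**Working it through.** **Inputs from the protocol article**

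- Per-test error 0.05, two-sided (Primary aim).
- Two visits tested, weeks 8 and 26 (Primary aim).
- Four scores: total plus three subscales (Primary aim, with the subscales listed under Primary outcome measure).
- Two arms, so one treatment contrast per ANCOVA (Study design).

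**Assumptions, because the documents give no figures**

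- Correlation between subscales: 0 to 0.8.
- Correlation between weeks 8 and 26: 0.3 to 0.8.
- Subscale standard deviations in the ratio 6:6:10. Equal standard deviations give nearly the same result (22.6% against 22.5% at correlations of 0.5).

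**Step 1: the plan's own figure.** One two-sided test at 0.05 has a type I error of 5.0%. This is the rate if PANSS total at week 26 is the only primary test.

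**Step 2: upper reference under independence.** The chance of at least one false positive in k independent tests is 1 − 0.95^k.

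- k = 2: 1 − 0.95² = 9.75%
- k = 4: 1 − 0.95⁴ = 18.5%
- k = 8: 1 − 0.95⁸ = 33.7%

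The last two cannot be reached here, because PANSS total is the sum of its subscales.

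**Step 3: correlated tests.** Under no effect, the three subscale test statistics at two visits were drawn as multivariate normal (500,000 draws per scenario). The total was built as their SD-weighted sum, and each statistic was compared with ±1.96.

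| What counts as a primary success | Both correlations 0.5 | Range over the grid |
|---|---|---|
| PANSS total, week 26 only | 5.0% | 5% |
| PANSS total, weeks 8 and 26 | 9.1% | 7.8–9.5% |
| Total and three subscales, week 26 only | 12.9% | 9.9–16% |
| Any of 4 scores × 2 visits | 22.5% | 15–29% |

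In the last row, the low end (15.0%) is at subscale and visit correlations of 0.8. The high end (28.7%) is at a subscale correlation of 0 and a visit correlation of 0.3. With subscale correlations of 0.3–0.6 and visit correlations of 0.3–0.7, the range narrows to 19–26%.

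**Step 4: does the Dunnett step change this?** No. Dunnett's test adjusts for several arms against one control. With two arms there is one contrast and nothing to adjust. The step is redundant and neither inflates nor controls error across scores or visits.

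**The case against.** The case for leaving the text alone has real content.

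- **A priority is already stated.** The Primary outcome measure section singles out the week 26 change and defines it from PANSS total, and the Primary aim section opens with a 26-week aim. A reader who gives these precedence has one test at 5%. This stands for week 26 and makes week 8 the weaker part of the conflict. It does not remove the conflict over the score, because the analytic plan expressly places the subscales in the primary outcome.
- **Eight primary tests is an inference.** The ANCOVA sentence refers to PANSS scores without listing subscales. The count comes from combining it with the sentence on total and subscale scores. No sentence says that any one significant result would be a primary success. This stands. A reader might infer that the trial's false-positive rate is 20–25% instead of 5%, but the documents do not support that as a fact: it needs the widest reading and correlations that they do not give.
- **The responder cut-offs are not shown to be primary tests.** They are offered as an alternative view of efficacy and are given no test or alpha. This stands, and they are not counted above.
- **The Dunnett step is harmless, and is not offered as protection across scores or visits.** This also stands. It is not part of the case.
- **A testing hierarchy is commonly left to a statistical analysis plan.** True, so its absence alone would be no finding. Two incompatible definitions in one document are a different matter.

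**Conclusion.** The point holds as a conflict of definition that should be resolved before unblinding. The error rate of a primary claim is 5% if the Primary outcome measure section governs. It is about 8–9.5% with PANSS total at both visits, about 10–16% with four scores at week 26, and about 15–29% if any of eight results may count. Every figure above 5% depends on assumed correlations and on treating any one significant result in the set as success. That the conflict exists is certain from the text; which of these rates applies is not.

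**What to change.** Align the Primary aim section with the Primary outcome measure section:

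- State that the sole primary test is the ANCOVA of PANSS total change from baseline to week 26, adjusted for baseline PANSS total, two-sided at 0.05, which matches the single 0.05 in the sample size.
- Label week 8, the subscales and the responder comparisons as secondary, with no primary claim.
- As tidying only, delete the Dunnett step.

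**Cost.** Wording only: no added patients and no loss of power for the week 26 total. The downside is that a positive subscale or week 8 result can no longer be claimed as primary.

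**The alternative is expensive.** Keeping all eight tests primary under Bonferroni would need 0.05/8 = 0.00625 per test. Take the planned effect of 0.3 as Cohen's f (a standardised difference of 0.6, an assumption), with baseline explaining 25% of variance and 36 per arm. The noncentrality is then 0.6 / (√0.75 × √(2/36)) = 2.94 on 69 degrees of freedom. Power for any one test falls from about 83% at 0.05 to about 55% at 0.00625.

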### Participant sample

The intended study population is composed of inpatients admitted to the Psychiatric Clinics of the Central Teaching Hospital, Medical University of Lodz. Patients will be enrolled consecutively as they are admitted to the hospital. Eligible patients will be (1) aged 16–35, (2) diagnosed with first-episode schizophrenia according to the International Classification of Diseases 10th version (ICD-10), which is an obligatory classification of mental disorders in Poland, (3) currently psychotic as reflected by the presence of at least one psychotic symptom daily for more than one week (delusions, hallucinations, disorders of thought form other than simple acceleration or retardation, and disorganized, bizarre, or markedly inappropriate behavior). Diagnosis will be confirmed by the mini neuropsychiatric interview plus (MINI plus) [53]. Patients will be excluded if more than two years have passed since the onset of positive symptoms, if the patient have bleeding disorders, or have been taking fish oil supplements or anticoagulants for any reason, were diagnosed with drug-induced psychosis, first-episode mania or organic disorders presenting with psychotic symptoms, if the patient has a history of intellectual disability, or a history of head injury with loss of consciousness, or any acute or unstable medical condition.

The trial procedures will be explained verbally and in writing to all eligible patients. All participants will provide written informed consent prior to study enrollment. The study will be conducted in accordance with the Declaration of Helsinki and the study protocol has been approved by the Ethics Committee of the Medical University of Lodz.

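### Duration of untreated psychosis and baseline diet are both singled out for statistical use, but neither is in the stated outcome model; this causes no bias but may forgo some precision and leaves two sections unreconciled

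*Protocol article*

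**What the plan says.** All references are to the protocol article.

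- **Baseline comparison (Statistical methods and analytic plan, Primary aim).** The arms are compared before treatment by a one-way ANCOVA, which is specified "with intervention type as a term in the model and duration of untreated psychosis (DUP) as covariate". This is the only place where duration of untreated psychosis (DUP) is named. The same paragraph says that socio-demographic characteristics will be compared to judge how well randomisation worked.
- **Outcome model (same section).** PANSS change to week 8 and to week 26 is analysed by ANCOVA "with intervention type as term and baseline PANSS score as covariate". For the other scales, "The same analyses will be repeated to assess the significance of differences in changes of CDSS, CGI and GAF scores". No further covariate is named.
- **Diet (The second secondary aim).** Diet is assessed once, at the start of the study. The stated reason is: "This will enable control of that possible confounder at the level of statistical analysis". Table 1 shows the diet history questionnaire at week 0 only. Neither the Primary aim nor the Secondary aim analysis has a diet term.
- **Entry limit (Participant sample).** "Patients will be excluded if more than two years have passed since the onset of positive symptoms".
- **Sample size (Power calculation).** 36 per arm for 80% power, effect size 0.3, two-sided 5% level, baseline scores assumed to explain 25% of outcome variation.

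**The concern.** Two baseline variables are picked out for statistical use. DUP is used as a covariate, but only in a model that compares the arms before treatment. Under sound randomisation any difference found there is due to chance, and adjusting it for DUP adds nothing to the estimate of the treatment effect. Diet is called a possible confounder to be handled in the analysis, but no analysis handles it.

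The article itself makes diet relevant. The Background reports that declared PUFA intake differs between first-episode patients and healthy controls. The Rationale for intervention arms suggests that n-3 food or supplements taken during an earlier trial may explain a rise in membrane PUFA in both of its groups. The Discussion concedes that red-cell n-3 cannot be measured here.

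Two things are at stake. If either variable predicts PANSS change beyond baseline PANSS, the plan gives up precision that data collected at baseline could supply. And a reader of the final report could not tell from this article whether a diet-adjusted result was planned, or which one.

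**Working it through.** **Step 1. Set the statements side by side.**

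| Variable | Baseline comparison | PANSS change model | CDSS, CGI, GAF change | Other statement |
|---|---|---|---|---|
| Baseline score | – | covariate (PANSS) | same analyses repeated | 25% of outcome variance (Power calculation) |
| DUP | covariate | not named | not named | none |
| Diet | not named | not named | not named | control at analysis (The second secondary aim) |

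**Step 2. Reproduce the stated sample size.** Inputs from Power calculation: f = 0.3, R² = 0.25, two-sided alpha 0.05, n = 36 per arm (N = 72). Reading 0.3 as Cohen's f (d = 0.6) is my assumption, because the article does not name the metric. I use the ANCOVA F test with 1 and N − 2 − k degrees of freedom (k covariates) and noncentrality λ = N·f²/(1 − R²).

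- λ = 72 × 0.09/0.75 = 8.64, with 1 and 69 degrees of freedom. Power is 82.6%.
- The smallest n giving 80% is 34 per arm, close to the stated 36.
- Read as Cohen's d, 0.3 would need 131–132 per arm and give about 31% power at 36, so that reading does not reproduce the plan.

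The stated power is therefore met with baseline score as the only covariate.

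**Step 3. Add DUP and one diet variable (k = 3, 67 residual degrees of freedom).** The article gives no figure for how much variance they explain beyond baseline PANSS, so the extra R² is an assumption, shown as a range that includes zero. The SE ratio is √[(1 − R²)/0.75].

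| Extra R² (assumed) | Total R² | λ = 72 × 0.09/(1 − R²) | Power | SE against plan | n per arm for 80% |
|---|---|---|---|---|---|
| plan as written (k = 1) | 0.25 | 8.64 | 82.6% | – | 34 |
| 0 | 0.25 | 8.64 | 82.6% | no change | – |
| 0.02 | 0.27 | 8.88 | 83.6% | −1.3% | 33 |
| 0.05 | 0.30 | 9.26 | 85.1% | −3.4% | 32 |
| 0.10 | 0.35 | 9.97 | 87.5% | −6.9% | 30 |

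**Step 4. Cost if the variables are not prognostic.** To four decimals, power goes from 0.8260 to 0.8256, a loss of 0.04 percentage point from two lost degrees of freedom.

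**Step 5. Gain.** 85.1 − 82.6 = 2.5 points at +0.05, and 87.5 − 82.6 = 4.9 points at +0.10. It is nil if the extra R² is nil.

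**The case against.** The planned model is sound as it stands. It is a pre-specified ANCOVA with the covariate most directly tied to the outcome, and the sample size relies on that covariate alone. Leaving out DUP and diet does not bias a randomised comparison. Nothing in the article shows that either predicts PANSS change, and the two-year limit on symptom duration narrows the spread of DUP and may limit its value. The diet sentence says that the data will enable control, which is weaker than a commitment to adjust. It stands under a secondary aim, and a secondary or sensitivity analysis would satisfy it. A separate analysis plan may say more.

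Most of this stands, and it limits the point. A reader might infer three stronger claims that the article does not support:

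- *That precision is being wasted.* This needs a known prognostic strength for DUP or diet, and none is given.
- *That covariates will be chosen after baseline p-values are seen.* The article does not link the baseline comparison to covariate choice, and it fixes the outcome covariate in advance. For socio-demographic variables it does not even state a significance test.
- *That a promise to adjust for diet is broken.* The wording only says that adjustment becomes possible.

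The objection does not remove the core. The outcome model is written out in full, DUP is assigned to a different model in which it has no use, and a purpose is stated for diet that no written analysis serves. That is a matter of what the text fixes, and goes beyond detail left to a later document.

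**Conclusion.** The point holds in a limited form. DUP serves only a baseline comparison that does not inform the treatment effect. Diet is described as controllable at analysis but appears in no model. The two statements need to be reconciled.

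The consequence is possible inefficiency, with no bias and no shortfall against the stated power. On the Cohen's f reading with 36 per arm, adding both variables changes power by between nil and about 5 percentage points for an assumed extra R² of 0 to 0.10. The true value is unknown and may be small. The case for changing the plan rests on asymmetry: the possible gain is modest, while the loss if both variables are useless is under 0.1 point.

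**What to change.** Before unblinding:

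1. State the week-26 PANSS total ANCOVA with treatment, baseline PANSS total, DUP and one dietary n-3 measure defined in advance from the baseline questionnaire. Fix the form in which each enters. If diet is to stay out of the primary model, name a diet-adjusted sensitivity analysis instead and refer to it where the dietary assessment is described.
2. Include the same variables in the multiple imputation model, so that imputation and analysis agree.
3. Replace the DUP-adjusted baseline ANCOVA with a descriptive table by arm, and describe the socio-demographic characteristics in the same way.

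The cost is a few sentences in the plan and one degree of freedom per covariate. No new data are needed: the diet questionnaire is scheduled at week 0, and DUP is already required for the planned baseline comparison.
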